### **9.2.3 Serious Adverse Device Effects (SADEs)**

Unexpected adverse device effects are SADEs if the following three conditions are met:

- the event must be serious (see Section 9.2.2);
- there must be a certain degree of probability that the event is a harmful and an undesirable reaction to the medical device described in section 6.1.
- the event must be unexpected, that is, the nature and severity of the event are not in agreement with the device information as reported in the IFU.

SADEs must be reported to the sponsor within 24 hours of first knowledge. The sponsor will report all SADEs through the web portal *ToetsingOnline* to the accredited METC that approved the protocol, within 7 days of first knowledge for SAEs that result in death or are life threatening followed by a period of maximum of 8 days to complete the initial preliminary report. All other unexpected SAEs will be reported within 15 days after the sponsor has first knowledge of the serious adverse events.

#### **9.2.4 Suspected unexpected serious adverse reactions (SUSARs)**

Not applicable.

### **9.3 Annual safety report**

Not applicable.

### **9.4 Follow-up of adverse events**

All AEs will be followed until they have abated, or until a stable situation has been reached. Depending on the event, follow up may require additional tests or medical procedures as indicated, and/or referral to the general physician or a medical specialist. SAEs need to be reported till end of study within the Netherlands, as defined in the protocol

### **9.5 Data Safety Monitoring Board (DSMB)**

An independent Data and Safety Monitoring Board (DSMB) will oversee the safety of patients in the trial. They will work in accordance with a dedicated charter and will follow processes recommended by the DAMOCLES statement. The DSMB will meet in person or online at least annually. An independent statistician will perform unblinded interim analyses as described under 10.5. The independent statistician will report the outcome of the interim analyses directly to the DSMB, as well as listings of all SAE reports and unblinded aggregate summaries of data by treatment group for review in closed meetings. Feedback, blind to treatment, will be provided in written conclusions to the sponsor and the B-STARS2 project leaders. Should the sponsor decide not to fully implement the advice of the DSMB, the sponsor will send the advice to the reviewing METC, including a note to substantiate why (part of) the advice of the DSMB will not be followed.

## **10. STATISTICAL ANALYSIS**

### **10.1 Statistical analysis plan**

The analysis and reporting of the trial will be in accordance with CONSORT guidelines. Before follow-up will have been completed, a statistical analysis plan (SAP) will be developed that will specify: (i) Hypotheses to be tested; (ii) Treatment effects to be estimated in order to satisfy the primary and secondary objectives of this trial; (iii) Technical description of the statistical methodology and procedures for performing the statistical analysis of outcome measures and SAE data; (iv) Primary, secondary, and sensitivity analyses; and (v) Subgroup analyses. The final SAP will be published before the first patient is included in the trial. The SAP will be signed off by the trial Executive Committee (Appendix C) and the trial statistician

and then published. The final statistical analyses will be performed once recruitment has ceased, final follow-up has been completed, final data have been checked and any errors corrected, and the database has been locked.

All analyses will be performed according to the intention-to-treat (ITT) principle. Baseline data by treatment allocation will be reported with statistical procedures. Missing values for baseline characteristics will be reported. Missing baseline characteristics will be imputed using multiple imputation.

### **10.2 Primary study parameter(s)**

The primary outcome is the FM-UE score at 90 days poststroke. The FM-UE reflects upper limb impairment on an ordinal scale from 0 (maximum impairment) to 66 points (no impairment). The primary analysis is performed using a linear mixed model in the intention-to-treat population, including all randomized subjects who started at least one cTBS session. Missing data are assumed to be missing at random and a FM-UE score of 0 will be assigned in case of death. The model includes at least the baseline FM-UE score; the stratification factor (ability versus no ability to extend one or more fingers), age, stroke subtype (ischemic stroke vs. intracerebral hemorrhage), and treatment (sham cTBS; active cTBS). The model includes a random effect for rehabilitation center.

#### Sensitivity analyses

Sensitivity analyses will be performed in the per-protocol population (defined as those in whom a valid FM-UE score could be assessed at 90 days post-stroke and who completed at least eight cTBS sessions).

#### Subgroup analyses

Predefined subgroup analyses will be based on baseline FM-UE extremity score (FM  $\leq 20$  versus FM  $> 20$ ); stroke subtype (ischemic stroke versus intracerebral hemorrhage); stroke location (cortical versus subcortical versus brainstem); time to start of treatment (within 14 days versus 15 to 21 days). Additional subgroup analyses may be described in the statistical analysis plan.

### **10.3 Secondary study parameter(s)**

Secondary endpoints are the FM-UE at 12 months post-stroke and the ARAT, NHPT, mRS, SIS-hand, SIS-participation and the EQ-5D at 90 days and 12 months post-stroke. These secondary endpoints are analyzed using a mixed model repeated measures or cumulative link mixed model, depending on the nature of the outcome measure. The model includes the baseline score; the stratification factor (ability versus no ability to

extend 1 or more fingers), visit (90 days and 12 months post-stroke), and the interaction of treatment (sham cTBS; active cTBS) by visit. The model includes a random effect for rehabilitation center. Additional model parameters and predefined subgroup analyses are described in the SAP.

The length of stay will be analyzed using a two-sample independent t-test.

Ipsilesional excitability will be analyzed using a linear mixed model. The outcome variable is the ipsilesional RMT after the final cTBS session. The model includes fixed effects for the ipsilesional RMT before the first cTBS session, stratification factor (ability versus no ability to extend 1 or more fingers) and treatment (sham cTBS; active cTBS) and a random effect for rehabilitation center.

Contralesional excitability before the 1st, 6th and 10th cTBS session will be analyzed using a mixed model for repeated measures. The outcome variable is the contralesional RMT determined before the 1st, 6th and 10th cTBS session. The model includes fixed effects for baseline RMT, cTBS session number (1, 6 or 10) and type of treatment (sham cTBS; active cTBS) and a random effect for rehabilitation center.

Contralesional inhibition after the 1st, 6th and 10th cTBS session will be analyzed using a mixed model for repeated measures. The outcome variable is the contralesional MEP amplitude after cTBS. The model includes fixed effects for and the contralesional MEP amplitude, cTBS session (1, 6 or 10) and treatment (sham cTBS; active cTBS) and a random effect for rehabilitation center.

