#### 4.4 Sample size calculation

The required sample size to test our hypothesis (superiority) in two groups is 440 subjects, based on a two-sided two-sample t-test power calculation with a minimal detectable effect of 6.6 points on the FM-UE scale (10% of the maximum score of 66, a mean score at 90 days of 42 and a standard deviation of 23 (calculated from the B-STARS trial data), a statistical significance level of 0.05 and statistical power of 0.85 (G\*power 3).

A study that specifically examined clinically important differences of FM-UE scores in stroke patients found that these ranged from 4.25 to 7.25 points, depending on the different facets of UE movement. A minimal clinically important difference of 6.6 points (10% of the maximum score FM-UE score) is in line with the module 'Noninvasive brain stimulation with rTMS' for the Dutch guideline 'Ischemic stroke and intracerebral hemorrhage'.

To compensate for possible loss to follow-up, we will include 454 patients. This sample size is also sufficient to demonstrate a treatment effect on secondary outcome measures. For example, for the ARAT, which tests upper limb-specific activity, a sample size of at least 396 would be required, based on a minimal clinically important difference of 5.7 and a mean score and standard deviation of 30 and 23, respectively (calculated from the B-STARS trial data), a statistical significance level of 0.05, and a statistical power of 0.8 (gigacalculator.com).

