##### *Baseline neurological and functional status*

FM-UE, ARAT, NHPT, mRS, SIS, BI, EQ-5D-5L, ability to extend 1 or more fingers of the paretic arm, motricity index,

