### **Nine Hole Peg Test (NHPT)**

The NHPT examines fine motor skills and manual dexterity. The patient must put 9 pegs into slots and individually place them back into a bin as quickly as possible with the affected hand. The test's outcome is the execution duration, with a maximum duration of 50 seconds, and the number of pegs that have been moved (within the 50 second time window), with a maximum of 18 points (1 point per peg movement). Reliability and validity have been demonstrated in stroke patients.

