### 7.5. Secondary analyses

The FM-UE, ARAT, NHPT, mRS, SIS-hand and SIS-participation and EQ-5D-5L at 90 days and 12 months post-stroke will be assessed using a mixed model for repeated measures or cumulative link mixed model, depending on the type of outcome measure. The outcome variable is the secondary outcome. The model includes fixed effects for the corresponding baseline scores; the stratification factor (ability versus no ability to extend one or more fingers), age, gender, stroke subtype (ischemic stroke vs. Intracerebral haemorrhage), visit (90 days; 12 months) and the interaction of treatment (sham cTBS; active cTBS) by visit and random effects for rehabilitation centre.

The length of stay will be analysed using a two-sample independent t-test.

Ipsilesional excitability will be analysed using a linear mixed model. The outcome variable is the ipsilesional RMT after the final cTBS session. The model includes fixed effects for the ipsilesional RMT before the first cTBS session, stratification factor (ability versus no ability to extend 1 or more fingers) and treatment (sham cTBS; active cTBS) and random effects for rehabilitation centre.

Contralesional excitability before the 1st, 6th and 10th cTBS session will be analysed using a mixed model for repeated measures. The outcome variable is the contralesional RMT determined before the 1st, 6th and 10th cTBS session. The model includes fixed effects for baseline RMT, cTBS session

number (1, 6 or 10) and type of treatment (sham cTBS; active cTBS) and random effects for rehabilitation centre.

Contralesional excitability after the 1st, 6th and 10th cTBS session will be analysed using a mixed model for repeated measures. The outcome variable is the contralesional MEP amplitude after cTBS. The model includes fixed effects for the contralesional MEP amplitude before cTBS, cTBS session (1, 6 or 10) and treatment (sham cTBS; active cTBS) and random effects for rehabilitation centre.

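### Secondary models for the ARAT and Nine Hole Peg Test leave out baseline FM-UE, which is already collected and is in the primary model; some precision is probably forgone, by an amount the documents cannot fix

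*Combined protocol and SAP*

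**What the plan says.** Protocol 10.3 covers the FM-UE at 12 months and the ARAT, NHPT, mRS, SIS-hand, SIS-participation and EQ-5D at 90 days and 12 months. Its covariate list begins "The model includes the baseline score; the stratification factor (ability versus no ability to" extend fingers), and continues with visit, treatment by visit and a random centre effect. It leaves further model parameters to the SAP.

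SAP 7.5 says for the same outcomes: "The model includes fixed effects for the corresponding baseline scores; the stratification factor", and adds age, gender and stroke subtype. Both texts allow either a mixed model for repeated measures or a cumulative link mixed model, according to the type of outcome. Neither says which scale gets which.

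Baseline FM-UE is in the planned baseline set (protocol 8.1.3): "FM-UE, ARAT, NHPT, mRS, SIS, BI, EQ-5D-5L, ability to extend 1 or more fingers of the paretic arm". It is a fixed effect in the primary model (protocol 10.2, SAP 7.4) and defines a severity subgroup (protocol 10.2, SAP 7.7). It enters only one secondary clinical-scale model, that for the 12-month FM-UE, where it is the corresponding baseline.

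**The concern.** Eligibility admits a motricity index as low as 9, and randomisation is stratified on whether the patient can extend even one finger. Patients with little or no hand function are therefore expected. On the NHPT the score is the time, capped at 50 seconds, and "the number of pegs that have been moved (within the 50 second time window), with a maximum of 18 points". A patient who cannot handle a peg scores 0 pegs at 50 seconds however well the shoulder and elbow move. Among such patients the own-baseline covariate is nearly constant, and finger extension is a single yes/no item that cannot rank them. The FM-UE, with 33 tasks and a range of 0 to 66, can still do so.

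If baseline FM-UE predicts later arm function beyond the planned covariates, leaving it out makes the treatment estimates for activity and dexterity less precise than the collected data allow. The ARAT matters most here, because it is the secondary outcome that protocol 4.4 uses to argue that the sample size is sufficient.

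**Working it through.** **1. The plan's own figures.** For the primary outcome, protocol 4.4 gives a "two-sided two-sample t-test power calculation", a "minimal detectable effect of 6.6 points on the FM-UE scale", "a mean score at 90 days of 42 and a standard deviation of 23", and "a statistical significance level of 0.05 and statistical power of 0.85". The normal approximation gives n per arm = 2 × [SD × (z₁ + z₂) / δ]² = 2 × [23 × (1.960 + 1.036) / 6.6]² = 218.1, so 219 per arm and 438 in total. The exact t-test gives 440, as stated.

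For the ARAT, protocol 4.4 states 396 from a difference of 5.7, SD 23, significance level 0.05 and power 0.8, without giving sidedness.
- Two-sided: 2 × [23 × (1.960 + 0.842) / 5.7]² = 255.6, so 256 per arm and 512 in total (514 by t-test).
- One-sided: 404 in total, near but not equal to 396.
- Two-sided power at 440 with the unadjusted SD: standard error = 23 × √(2/220) = 2.193, and Φ(5.7/2.193 − 1.960) = 0.74.
- Reaching 80% at 440 needs an SD of 21.34. The covariates must then explain 1 − (21.34/23)² = 14% of the ARAT variance.

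The 396 is a separate matter. It bears on this point only because it shows that two-sided ARAT power depends on how much the covariates explain.

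**2. Effect of adding a covariate.** Let R² be the share of outcome variance explained by the planned covariates, and p the share of the remainder that baseline FM-UE explains. In a linear model the residual SD is 23 × √[(1 − R²)(1 − p)], so the standard error is multiplied by √(1 − p). The documents give neither R² nor p. With 220 per arm, a difference of 5.7 and a two-sided test:

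| p | Standard error reduction | Power if R² = 0.3 | Power if R² = 0.5 |
|---|---|---|---|
| 0 | none | 0.874 | 0.957 |
| 0.02 | 1.0% | 0.881 | 0.960 |
| 0.05 | 2.5% | 0.890 | 0.965 |
| 0.10 | 5.1% | 0.906 | 0.972 |
| 0.20 | 10.6% | 0.935 | 0.984 |

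**3. Plausible values of p for the ARAT.** These come from simulation, and every input below is an assumption.
- *One underlying trait.* Baseline FM-UE, baseline ARAT and finger extension are noisy readings of one arm-function trait. Between 30% and 60% of patients are at the baseline ARAT floor, and the trait correlates 0.6 to 0.85 between baseline and 90 days. With own baseline and finger extension in the model, p runs from 0.02 to 0.16, the standard error falls by 1.2 to 8.5%, and power rises by about 1 to 4 points.
- *The same runs without finger extension.* p is 0.04 to 0.26, so the planned stratification factor already recovers roughly 35 to 45% of what FM-UE would otherwise add.
- *Separate proximal and distal traits* (floor about 16 to 43%). With the two traits correlated 0.85, p is about 0.005 to 0.11; at 0.7, about 0.001 to 0.06. One-trait runs in this set-up gave 0.02 to 0.20.

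The gain thus depends on how closely the FM-UE tracks the ability that the ARAT measures, which the documents do not report. None of these ranges is a hard bound, and the simulated models omit age, gender, stroke subtype and centre.

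**The case against.** The strongest reply is that the plan is already coherent. Own baseline plus a stratification factor that directly marks hand function is a defensible pre-specified choice. The SAP adds three further covariates, and the primary analysis already uses baseline FM-UE. Nothing here affects bias, type I error or the primary result. All of that stands, and it limits the point to a modest gain in efficiency.

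Four stronger readings are tempting, and the documents do not support them.
- *That each secondary model adjusts only for its own baseline score.* Finger extension, age, gender and stroke subtype are also included, and the 12-month FM-UE model does contain baseline FM-UE.
- *That patients without hand function sit at the floor of both tests.* No baseline distribution is reported. The ARAT includes gross movements (protocol 8.3), so proximal ability can score. The floor argument is sound in principle for the NHPT and weaker for the ARAT.
- *That the gain can be stated as a definite percentage or as a number of patients saved.* It rests on assumed correlations, and the lower end is close to zero once proximal and distal function are allowed to differ.
- *That standard errors shrink in every secondary model.* In a cumulative link model, a prognostic covariate changes the conditional odds ratio itself. In one illustrative ordinal-logit check the log odds ratio moved from 0.341 to 0.374 while its standard error rose slightly, from 0.0255 to 0.0257. The ratio of estimate to standard error still improved (13.4 to 14.6), but the variance argument above does not describe that case.

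What remains is that an already collected, plausibly prognostic covariate is left out of the ARAT and NHPT models, and no reason is given.

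**Conclusion.** The point holds as a modest, low-cost improvement. Baseline FM-UE is absent from the secondary models of all the non-FM-UE clinical scales in both documents. Some precision is probably forgone, mainly for the ARAT and NHPT.

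For the ARAT, the assumed scenarios give a reduction in residual variance from under 1% to about 16%, with a standard error roughly 0 to 9% smaller. This rests on linear models, an assumed baseline floor and assumed correlations. The NHPT case rests on the structure of the test and has no firm figure. SIS-hand was not simulated, and no size can be given for the mRS, SIS-participation or EQ-5D-5L. The planned analyses remain valid without the change.

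**What to change.** Before unblinding, add baseline FM-UE to SAP 7.5 as a fixed effect in the ARAT and NHPT models, next to the corresponding baseline score, and mirror this in protocol 10.3. Extending it to SIS-hand is reasonable. For the mRS, SIS-participation and EQ-5D-5L it is optional. The 12-month FM-UE model needs no change.

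The same edit should state which scales are analysed with a cumulative link model, since the estimate there becomes conditional on one more covariate and should be reported as such.

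The cost is a line of SAP text and one degree of freedom per model, with no new data. The SAP change log shows that gender was added as a fixed effect by the same route in version 3.

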### **Contralesional corticospinal excitability**

Corticospinal excitability is determined based on the RMT (defined under section 5.1). The contralesional RMT is assessed before the 1st, 6th and 10th cTBS session, as part of the treatment procedure described under section 5.1. Therefore, it does not require additional measurements.

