## 1. Study objectives

Primary Objective:

- To assess whether 10 sessions of cTBS of the contralesional primary motor cortex (M1) combined with regular care upper limb training, started within three weeks after stroke onset and continued every working day for two weeks, reduce upper limb impairment at 90 days after stroke, compared to sham stimulation.

Secondary Objective(s):

To assess whether 10 sessions of cTBS of the contralesional M1 combined with regular care upper limb training, started within three weeks after stroke onset and continued every working day for two weeks:

- improve upper limb activity, manual dexterity and quality of life, and reduces disability and dependence at 90 days and 12 months after stroke, compared to sham stimulation;
- reduce upper limb impairment at 12 months after stroke, compared to sham stimulation;
- are cost-effective compared to sham stimulation;
- reduce excitability of the contralesional M1 during the 2-week treatment period, compared to sham stimulation;
- increase ipsilesional M1 excitability after 10 treatment sessions, compared to sham stimulation.

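### The contralesional RMT model counts the pre-stimulation session-1 value both as an outcome and as the baseline covariate, so with equal session weights its treatment effect is one-third too small

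*Combined protocol and SAP*

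**What the plan says.** One secondary objective in both documents is to show that active stimulation will "reduce excitability of the contralesional M1 during the 2-week treatment period, compared to sham stimulation" (SAP 1; also protocol 2). Table 1 of each document measures contralesional excitability by the RMT, taken ahead of sessions 1, 6 and 10.

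The model is the same in both documents:

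- **Outcome.** SAP 7.5: "The outcome variable is the contralesional RMT determined before the" first, sixth and tenth sessions.
- **Fixed effects.** Protocol 10.3: "The model includes fixed effects for baseline RMT, cTBS session number (1, 6 or 10) and type of treatment (sham cTBS; active cTBS". SAP 7.5 has the same terms, baseline RMT among them: "number (1, 6 or 10) and type of treatment (sham cTBS; active cTBS) and random effects for rehabilitation". Session has three levels, so session 1 is a row of outcome data. Treatment enters as a main effect only.
- **Random part.** Protocol 10.3 ends the list with "and type of treatment (sham cTBS; active cTBS) and a random effect for rehabilitation center". Neither document names a within-patient covariance structure for this model.
- **Source of the baseline.** Protocol 8.3 says that the contralesional RMT is obtained "as part of the treatment procedure described under section 5.1. Therefore, it does not require additional measurements". Neither schedule of assessments lists a separate contralesional baseline RMT.

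**The concern.** Session 1's RMT is read before the first pulse train, so randomised treatment cannot have affected it. Under a common treatment coefficient, one of the three outcome rows per patient therefore carries a known zero effect. If that row is also the covariate, the covariate predicts it exactly.

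Other models in the same sections avoid this. The clinical secondary model uses follow-up visits only, with "visit (90 days and 12 months post-stroke), and the interaction of treatment (sham cTBS; active cTBS) by visit". The ipsilesional RMT model takes the value before the first session as covariate and the value after the last session as outcome. The contralesional RMT model is out of line with both.

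At stake is the reported size of the effect on a measure of the presumed mechanism (inhibition of the contralesional motor cortex, protocol 13.1). Without a treatment-by-session term, any build-up between sessions 6 and 10 is also hidden.

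**Working it through.** **The plan's own figure.** The documents give no effect size, SD or power for RMT. The only related figure is the trial size, used below as N. Protocol 4.4 has 6.6 points, SD 23, two-sided 0.05 and power 0.85. The normal formula gives 2 × (1.960 + 1.036)² × 23² / 6.6² = 218.1, so 219 per arm. The exact t-test gives 219.03, so 220 per arm and 440 in total, as stated.

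**Algebra.** Let d6 and d10 be the treatment effects at sessions 6 and 10. The session-1 effect is 0. Baseline and treatment are constant within a patient, so with complete data the treatment coefficient is a weighted mean of the three session-specific effects:

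- Weights: w = V⁻¹1 / (1′V⁻¹1), with V the within-patient covariance.
- Independent or compound-symmetry errors: w = (1/3, 1/3, 1/3). The coefficient is (0 + d6 + d10)/3 = 2/3 × (d6 + d10)/2.
- AR(1): session 1 has weight 1/(3 − ρ). This is 1/2.8 = 0.36 at ρ = 0.2 and 1/2.1 = 0.48 at ρ = 0.9. If d6 = d10, the estimate is cut by 36% to 48%.
- Unstructured: with baseline slope 1 and treatment effect 0, the session-1 residuals are exactly zero. The session-1 variance goes to zero and the likelihood has no proper maximum.

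Under compound symmetry the standard error scales by the same 2/3, so the ratio of estimate to standard error is nearly unchanged.

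**Simulation.** 300 trials, N = 440, 1:1, 16 centres. The RMT SD of 10 and within-patient correlation of 0.8 are assumptions, as are the effects. The fitted models left out the centre effect. Baseline is the session-1 value.

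| True effect at sessions 6, 10 | As written, compound symmetry | Sessions 6 and 10 only | Ratio |
|---|---|---|---|
| 3.0, 3.0 | 2.01 (SE 0.32) | 3.02 (SE 0.49) | 0.67 |
| 1.67, 3.0 | 1.56 (SE 0.32) | 2.35 (SE 0.48) | 0.66 |
| 1.2, 1.2 | 0.80 (SE 0.32) | 1.19 (SE 0.49) | 0.67 |

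- The fitted baseline slope is 0.871 as written and 0.806 for sessions 6 and 10 only. The algebra predicts (1 + 2 × 0.806)/3 = 0.871.
- Power for a true effect of 1.2 is 0.713 as written and 0.710 for sessions 6 and 10 only. Under no effect, both reject in 0.053 of trials.
- Where the effect builds up (second row), 1.56 is 48% below the session-10 effect of 3.0. Adding treatment-by-session to the post-baseline model recovers 3.03 at session 10.
- With independent errors the point estimate equals the compound-symmetry one, but the standard error is too small (0.28 against an empirical SD of 0.32) and the null rejection rate is 0.097.
- With unstructured covariance, the session-1 variance falls to the numerical floor, the slope goes to 1.000 and the treatment estimate to 0.0000, whatever the true effect.
- If baseline were a separate pre-treatment reading, a true 3.0 is estimated as 1.98, including under unstructured covariance. The one-third cut remains and the fit does not degenerate.

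**The case against.** **Baseline RMT is never defined.** Protocol 8.1.3 lists corticospinal excitability among the baseline values. The optional TMS disruption test, done at baseline in one centre, is set as a percentage of RMT. A separate reading is therefore conceivable. Protocol 8.1.2 also says that RMT is taken before every session, which conflicts with 8.3 but adds no separate baseline. This objection bears only on the degenerate fit. The one-third cut does not need the two values to be identical.

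**The test is hardly affected under compound symmetry.** This stands. In a second simulation (residual SD 4, true effect 2.0), the ratio of estimate to standard error is 1.33/0.23 = 5.8 as written and 1.99/0.34 = 5.9 after correction. The defect does not make the trial miss an effect.

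**Quality control may catch it.** SAP 5.3 requires a full run on dummy codes, with peer review of code, log and output. A zero session-1 variance does not depend on the treatment codes, so that run should expose it. It would not show the one-third cut.

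Three stronger readings are tempting, and the documents do not support them:

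- *The estimate will collapse to zero.* This needs an unstructured covariance, which neither document names. Even then the outcome is a failed fit, not a null finding likely to be reported.
- *The objective has no other analysis.* SAP 7.5 has a second contralesional excitability model, with motor-evoked potential amplitude after stimulation as outcome and amplitude before it as covariate. The measurement is optional in protocol 8.3, but it is planned.
- *The confidence interval will exclude the true effect.* That depends on assumed RMT figures. In the second simulation a true effect of 2.0 gives 1.33 ± 1.96 × 0.23, about 0.88 to 1.78, which excludes it. A true effect of 1.0 gives 0.68 ± 0.45, about 0.23 to 1.13, which includes it.

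**Conclusion.** The concern holds. As specified, the treatment coefficient does not estimate the effect of stimulation on contralesional RMT during treatment. With equal session weights it is two-thirds of the mean effect at sessions 6 and 10. That factor follows from the model and complete data, and does not depend on the assumed SD, correlation or effect size. Relative to session 10 alone, the shortfall is larger if the effect grows. Other covariance structures give other answers: a cut of 36% to 48% under AR(1) for ρ from 0.2 to 0.9 with equal effects, and a degenerate fit under an unstructured matrix. The result thus depends on a choice that the plan leaves open.

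Reading baseline as the session-1 value is an inference from both versions of Table 1 and protocol 8.3. The harm is to the size and meaning of one mechanistic secondary estimate and its interval. The primary FM-UE analysis and the clinical secondary models are unaffected. It should be corrected, but it does not threaten the trial's main conclusion.

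**What to change.** In protocol 10.3 and SAP 7.5:

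- Define baseline contralesional RMT as the value before session 1, and use it only as a covariate.
- Restrict the outcome to the RMT before sessions 6 and 10, so that session has two levels.
- Add a treatment-by-session interaction.
- State the target contrast, for example the session-10 effect or the mean over sessions 6 and 10.
- State the within-patient covariance structure.

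An equivalent route keeps session 1 as an outcome with a baseline mean common to both arms, drops the baseline covariate and includes treatment-by-session. Adding the finger-extension stratum would match the ipsilesional model, but it is optional and does not cure the defect.

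The cost is a few sentences in each document, with no new data. The change should be made before unblinding.
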